### Relevant concomitant care permitted or prohibited during the trial {11d}

No changes in LEDD are permitted during this study, and other concomitant care is not restricted during the course of this trial.

### Provisions for posttrial care {30}

Participants are able to continue with their preferred DBS stimulation settings after the trial and are referred back to their neurologist.

### Outcomes {12}

The primary outcome is the comparison of the Starkstein Apathy Score (SAS) score following 1 month of DBS on the original contact and the SAS score following 1 month of DBS on the more dorsal contact [19]. Secondary outcomes are symptom changes on the Movement Disorders Society-Unified Parkinson’s Disease Rating Scale motor part III (MDS-UPDRS-III) [20]. Montgomery-Åsberg Depression Rating Scale (MADRS) [21]. 39-item Parkinson’s disease questionnaire (PDQ-39) [22]. Parkinson’s Disease Impulsive-Compulsive Disorders Questionnaire (QUIP) [23]. changes in levodopa-equivalent daily dosage (LEDD) [24]. apathy rated by the caregiver (AES-I) [25]. and burden and quality of life of the caregiver (SF-36) [26]. Additionally, participants will be asked which program they thought contained the investigational settings (i.e., “first,” “second,” or “unsure”) and which program they wish to continue to use (i.e., first or second). The preoperative MRI, postoperative CT-scan, and preoperative SAS scores will be retrospectively collected to provide supplementary information about the relationship between apathy and stimulation location.

### Sample size {14}

We estimated that a mean change of 8 points on the SAS is clinically relevant based on three cases in our center and two other studies that focused on the treatment of apathy in PD [14, 18, 30]. For our power calculation, we calculated that the two-sided *t*-test will achieve 80% power to ascertain that the mean difference is not 0 SAS points, if the total sample size of a two-by-two cross-over design is 20. If the actual mean difference between the DBS settings is 8 SAS points, the standard deviation of the paired differences is 12, and the significance level is 0.05, and 21 patients are needed to reach statistical significance. We aim to include a total of 26 patients because we anticipate a dropout up to 20%, because apathy may be difficult to combine with participation in a time-demanding clinical trial.

### Recruitment {15}

Based on the number of patients operated every year (40–80), we estimate that the inclusion of 26 patients should be feasible [8].

## Assignment of interventions: allocation

### Sequence generation {16a}

Participants will be randomized (1:1) to arm A and B using website-based randomization.

### Concealment mechanism {16b}

The blinded assessor is a second nurse practitioner, who will perform the 1- and 2-month follow-up assessment. The blinded assessor will not be able to access the stimulation settings of the programmer but will be able to switch from the first to the second program after 1 month.

### Implementation {16c}

The randomization will be performed by one of the coordinating investigator or co-investigators in Castor, Electronic Data Capture, to conceal intervention allocation [31]. Participants will only be randomized after the baseline measurements have been registered.

## Assignment of interventions: blinding

### Who will be blinded {17a}

Both the participant and the assessor will be blinded in this trial.

### Procedure for unblinding if needed {17b}

Individual treatment codes will be available to the involved neurologist at the study center for breaking the blind for medical emergencies necessitating treatment randomization.

## Data collection and management

### Plans for assessment and collection of outcomes {18a}

The assessors of each participating center are trained by the coordinating center (Amsterdam UMC) for the assessment of the study instruments. The study instruments involve the following questionnaires: SAS, with acceptable validity [32]. MDS-UPDRS-III, with strong concurrent validity [20]. MADRS with good validity and reliability [33]. PDQ-39 with good validity and acceptable reliability [34]. QUIP with good validity [35]. AES-I with good reliability [32]. and SF-36 with good reliability and validity [36].

### Plans to promote participant retention and complete follow-up {18b}

Participants who wish to discontinue the study are allowed to quit at any time, and the reason for withdrawal will be recorded if possible.

### Data management {19}

The data collection forms can be requested in the form of digital forms or physical case report forms. Missing SAS values will be analyzed as missing or as imputed using multiple imputation using baseline covariates as independent variables, and other missing data will be deleted listwise.

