## Statistical methods

### Statistical methods for primary and secondary outcomes {20a}

The difference in SAS scores between dorsal DBS and standard care will be examined using a mixed-effects model with a random intercept per patient. The SAS scores will be dichotomized using the proposed cutoff of 14. The *χ*^2^ test will be used to determine whether there is a difference in apathetic individuals between the investigational phase and the control phase. All statistical programming and analysis will be performed using IBM SPSS statistics version 24 (IBM Corp., Armonk, NY, USA).

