### Methods in analysis to handle protocol nonadherence and any statistical methods to handle missing data {20c}

The main statistical analyses of the primary endpoint will be based on the intention-to-treat principle. In addition, we will perform a per-protocol analysis on data from patients with complete SAS data from every time point.

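### Missing SAS scores are left to an unresolved either/or, and the imputation route names only baseline covariates, which can shrink the treatment effect if scores are imputed by visit

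*Protocol article*

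**What the plan says.** The Data management section {19} of the protocol article sets the rule for missing scores on the primary outcome: "Missing SAS values will be analyzed as missing or as imputed using multiple imputation using baseline covariates as independent variables". For everything else, "other missing data will be deleted listwise".

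The Statistical methods section {20a} says that the difference in SAS "will be examined using a mixed-effects model with a random intercept per patient". Section {20c} adds that "The main statistical analyses of the primary endpoint will be based on the intention-to-treat principle", together with a "per-protocol analysis on data from patients with complete SAS data from every time point". Neither section says how a missing SAS score enters the intention-to-treat analysis.

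The Sample size section {14} says "we anticipate a dropout up to 20" per cent, on the ground that apathy may make participation hard. The Outcomes section {12} defines the primary comparison by stimulation condition, while the assessment schedule (Table 1) collects SAS by visit.

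**The concern.** First, the two routes for missing SAS are joined by an 'or', with no statement of which is primary. They can give different estimates of the treatment effect, so the choice matters.

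Second, the predictors named for the imputation are all measured before randomisation. A model with only those predictors does not know which setting the patient was on in the missing period, and it ignores that patient's score from the other period. In a crossover the within-patient contrast is the quantity of interest, and the other period's score is an obvious predictor. If leaving the trial depends on the visit 1 SAS, which the article's own reason for dropout makes plausible, the model also lacks the variable that would make a missing-at-random assumption credible.

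At stake is the primary estimate of a 26-patient trial whose calculated requirement is 20 or 21, so there is little spare power.

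**Working it through.** **Inputs.** From Sample size {14}: difference 8 SAS points ("If the actual mean difference between the DBS settings is 8 SAS points"), "the standard deviation of the paired differences is 12", two-sided 0.05, 26 enrolled, dropout up to 20%. From Sequence generation {16a}: 1:1 allocation. Assumed, because the article does not give it: within-patient correlation of SAS 0.3, 0.5 or 0.7.

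**The plan's own figure.** The noncentrality at N = 20 is 8/(12/√20) = 2.98. Exact power is 0.807 with 19 degrees of freedom and 0.805 with 18, so the stated 80% at N = 20 is reproduced. At N = 21 power is 0.828 or 0.826.

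**Expected attenuation under imputation by visit.** Let δ be the true difference and f the fraction with a missing visit 2, the same in both sequences. Without sequence in the model, the imputed visit 2 score is centred on the average of the two settings. That is δ/2 away from the patient's own visit 1 setting, whichever came first. An imputed patient therefore contributes δ/2 instead of δ:

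E(estimate) = (1 − f)δ + f·δ/2 = δ(1 − f/2)

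- 3 of 26 missing: 8 × (1 − 0.115/2) = 7.54
- 5 of 26 missing: 8 × (1 − 0.192/2) = 7.23
- 20% missing: 8 × (1 − 0.20/2) = 7.2

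If a patient misses both visits, both imputed scores have the same centre and the contribution is zero. The expectation is then δ(1 − f), or 6.4 at 20%.

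**Simulation.** N = 26, 5 patients missing visit 2 completely at random, 15 imputations, 600 replicates, period-adjusted 2×2 estimator. Each cell gives mean estimate / power.

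| Correlation | Complete pairs, no imputation | Baseline only, by visit | Baseline only, by condition | Baseline, sequence and visit 1 SAS |
|---|---|---|---|---|
| 0.3 | 7.96 / 0.827 | 7.26 / 0.757 | 8.04 / 0.855 | 8.06 / 0.822 |
| 0.5 | 8.22 / 0.835 | 7.25 / 0.728 | 7.89 / 0.813 | 8.06 / 0.803 |
| 0.7 | 8.08 / 0.847 | 6.97 / 0.667 | 7.89 / 0.767 | 7.93 / 0.815 |

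The simulation error is about 2.25/√600 = 0.09 for a mean and √(0.75 × 0.25/600) = 0.018 for a power. As a check, 26 − 5 = 21 complete pairs should have exact power 0.826, and the first column agrees within error.

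A repeat simulation under the same assumptions gave:
- by visit on baseline only: 7.15-7.25, power about 0.70-0.77;
- with sequence and visit 1 SAS: about 8.0, power about 0.80-0.85;
- by condition: 7.95-8.07;
- complete pairs: 7.9-8.0;
- by visit on baseline only, with 3 of 26 missing: about 7.6, close to the 7.54 from the formula.

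**All five dropouts missing both visits.** Imputation by visit on baseline only gives 6.3-6.4 with power 0.42-0.50. Imputation by condition gives 7.9-8.0 with power 0.70-0.71. Complete pairs give 7.9-8.0 with power 0.81-0.82.

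**The case against.** The strongest reply is that the loss needs three things at once: imputation is the primary route, the baseline covariates are the complete list of predictors, and scores are imputed by visit. The article states neither the first nor the third. On the second, it names no other predictor, but it does not say that there are none. Because Outcomes {12} defines the primary comparison by condition, imputing the dorsal and control scores as separate variables is a fair reading. Treatment then enters implicitly and the mean is right. That stands. A reader might infer that the planned analysis is biased towards no effect, but the documents do not support so flat a statement.

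It also stands that the handling recommended here is already one of the two routes. Leaving missing scores missing, in a random-intercept model under intention to treat, uses every observed score. Section {20c} reserves complete SAS data for the per-protocol analysis, which suggests that incomplete patients stay in the main one.

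The size must be kept in proportion. Five of 26 is close to the article's ceiling for dropout, and the figure of 6.4 applies only if every dropout misses both visits. Attenuation also works against a claim of benefit, so by itself it does not create a false one. Nor does the article show that the route would be picked after seeing results: an analysis plan that is not shown may settle it, or both analyses may be meant.

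What does not fall away is the text itself. It is a stated rule for the primary outcome, not an omitted detail. It leaves the primary route open, and the predictors it names permit the version that attenuates. Table 1 schedules SAS by visit, so imputing by visit is a natural way to carry the rule out.

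**Conclusion.** The concern holds in conditional form. The primary handling of missing SAS is not named, and the imputation as described can pull the effect towards zero. With only visit 2 missing, 8 becomes about 7.6 with 3 of 26 missing and about 7.2 with 5 of 26. In the latter case power is about 0.70-0.77, against about 0.80-0.85 with the fuller imputation model. On that reading, imputing is worse than analysing the complete pairs without imputation.

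These figures assume imputation by visit, dropout completely at random, a true difference of 8, an SD of differences of 12, and a correlation of 0.3-0.7. The attenuation disappears if imputation is by condition or if the mixed model is fitted to the observed scores. Imputing by condition on baseline covariates alone still discards the other period's score. This should be fixed, but it does not invalidate the design.

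**What to change.** In Data management {19} and section {20c}, replace the either/or with two sentences:

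1. The primary intention-to-treat analysis fits the random-intercept mixed model of section {20a} to all observed visit 1 and visit 2 SAS scores, without imputation. A patient with one of the two scores stays in the analysis.
2. Multiple imputation is a sensitivity analysis. Its model includes allocated sequence (or condition and period), the SAS from the other visit, and baseline SAS.

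The cost is those two sentences, with no extra data or visits. On the status reported in the article (16 of 26 participants finished, recruitment ongoing), the change can be made before the analysis.

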### Confidentiality {27}

All data concerning the subjects will be stored anonymously by a code that is unique for each subject. A subject identification code list will be kept by the principal investigator. The handling of personal data will comply with the Dutch Personal Data Protection Act. The local research institution will keep the source data for 15 years.

### Plans for collection, laboratory evaluation, and storage of biological specimens for genetic or molecular analysis in this trial/future use {33}

There will be no biological specimens collected.

## Statistical methods

### Statistical methods for primary and secondary outcomes {20a}

The difference in SAS scores between dorsal DBS and standard care will be examined using a mixed-effects model with a random intercept per patient. The SAS scores will be dichotomized using the proposed cutoff of 14. The *χ*^2^ test will be used to determine whether there is a difference in apathetic individuals between the investigational phase and the control phase. All statistical programming and analysis will be performed using IBM SPSS statistics version 24 (IBM Corp., Armonk, NY, USA).

### Interim analyses {21b}

No formal interim analysis on efficacy is planned.

### Methods for additional analyses {20b}

The SAS follow-up scores will be further investigated using McNemar tests, paired *t*-tests, and Wilcoxon signed-rank tests taking into account patients’ MDS-UPDRS-III, SAS, MADRS, QUIP, LEDD, PDQ-39, AES-I, and SF-36.

### Methods in analysis to handle protocol nonadherence and any statistical methods to handle missing data {20c}

The main statistical analyses of the primary endpoint will be based on the intention-to-treat principle. In addition, we will perform a per-protocol analysis on data from patients with complete SAS data from every time point.

### Plans to give access to the full protocol, participant-level data, and statistical code {31c}

De-identified participant data and statistical code are available on reasonable request, as is the full protocol.

## Oversight and monitoring

### Composition of the coordinating center and trial steering committee {5d}

The Amsterdam UMC center will coordinate the trial with day-to-day support for all centers with monthly meetings.

### Composition of the data monitoring committee and its role and reporting structure {21a}

There is no data and safety monitoring board because of the low expectance of safety concerns or risks for participants.

### Adverse event reporting and harms {22}

All adverse events reported spontaneously by the subject or observed by the investigator will be recorded and reported to the Medical Ethical Committee as required indicating expectedness, seriousness, severity, and causality.

### Frequency and plans for auditing trial conduct {23}

The independent Amsterdam UMC monitoring program will monitor this study for each participating center.

### Plans for communicating important protocol amendments {25}

The Medical Ethical Committee will be informed for any new protocol amendments and will be asked for approval.

### Dissemination plans {31a}

After completion of the study and data analysis, results will be made publically without restriction, independent of the outcome.

## Discussion

Patients suffering from PD often experience neuropsychiatric symptoms, which might even be the first detectable symptom of this neurodegenerative process [37]. DBS has great potential to relieve motor symptoms and may also have a beneficial effect on many non-motor symptoms [3, 27, 38]. One of the main challenges in the management of advanced PD and STN DBS is increased apathy after STN DBS with a high impact on quality of life [7]. The pathophysiology of apathy in PD, and particularly in the case of STN DBS, is still not fully understood; however, the relation between apathy and medication reduction and a direct stimulation effect are recognized as potential factors [9]. Because our proposed intervention is only a minor adjustment in the stimulation settings, this adjustment has the potential to improve the quality of life of many PD patients relying on STN DBS without many side effects. The application of STN DBS may subsequently be expanded as a patient’s mood might benefit from the treatment of invalidating PD motor and hypodopaminergic non-motor symptoms, as well as the possible reduction of hyperdopaminergic side effects that are allowed by lowered LEDD following STN DBS. The reduction of apathy might further increase physical health of people with PD who might have been limited in their activities by apathy and improve their social life. The study design has some limitations: first, the contact point that will be selected for the intervention will not be based on MRI imaging. This practice has been chosen because of the concept generalization; in this way, our intervention could be applied regardless of access to visualization of the STN subregions which are difficult to distinguish. The imaging of these subregions would preferably be done requiring imaging instruments on the level of 7-Tesla MRI scans, which is almost exclusively used for research and not clinical practice. Another argument for our decision was the desire to not influence the selection of intervention based on our hypothesis but to apply the intervention that has worked for previous patients [18]. However, this contact point was not necessarily closest to the motor region of the STN. Benefits of choosing the contact closest to the motor region of the STN on MRI imaging might have been the following: a more optimal motor response with possibly less required adjustments in LEDD or DBS current and less risk of stimulating adjacent regions with possible additional side effects. Second, we chose an apathy score of 14 or more on the SAS as inclusion criteria instead of an increased SAS score between pre- and postoperative assessments, which would more likely indicate solely STN DBS-induced apathy. Our argument for this decision was also generalizability because STN DBS-treated patients with apathy will have rarely available preoperative apathy scores for comparison. Furthermore, other studies found that STN DBS improved apathy or PD-related dysphoria without an earlier increase of apathy following STN DBS [39, 40]. Third, this study focused on apathy, although apathy is associated with other disorders. For example, apathy and depression share many features and might have some common pathophysiology when related to PD. We chose to include the most common disorders as secondary outcomes and not exclude participants with a current depressive or psychotic episode [3, 9, 41, 42]. Fourth, enrollment of participants was possible after only 3 months of STN DBS which might arguably be too soon because many centers optimize DBS stimulation and dopaminergic medication in the first 6 months. We chose the timepoint of at least 3 months because of four reasons: optimization of DBS and medication within 3 months are prioritized in our center, an earlier study showed that apathy did not further increase after 3 months [43]. cognitive decline might develop in the timespan of DBS surgery and optimization, and waiting on drugs for the treatment of depressive episodes to have effect was deemed inconsequential because this study aimed to treat apathy regardless of depressive symptoms. Fifth, 1 month of intervention is relatively short, we opted for this period because in our case study, and the direct stimulation effect was resolved within days to weeks [18]. This fast effect was also present in another case study [7]. To our knowledge, these are the only intervention reports on an imaging-supported STN DBS stimulation effect on apathy. However, relative to most non-motor symptoms and psychiatric disorders, an intervention of 1 month is short, and this could restrict the effectiveness of the trial. We hypothesize that switching stimulation to the motor region of the STN could be an optimization for DBS in PD, with an effect on multiple psychiatric symptoms and quality of life.

## Trial status

Recruitment started in February 2020 and is ongoing. Currently, 16 out of 26 participants have been included and finished follow-up (15th of January 2024).

Amendments are drafted after notifying the sponsor of changes to the protocol. The PI will notify the centers after approval by the Medical Ethical Committee and send a revised protocol to add to the Investigator Site File and the Clinical Trial Registry. Any deviations from the protocol will be fully documented using a protocol deviation form. The funder is notified yearly on the status of the trial including submitted amendments. Current approved amendments are as follows:Amendment 1.1 was submitted on 05 September 2019 and specified the assessment of the most ventrally stimulating electrode based on fused preoperative MRI and postoperative CT-scan imaging.Amendment 1.2 was submitted on 08 November 2019 by allowing for the inclusion of participants after 3 months after DBS surgery instead of 6 months and by allowing voltage or amperage adjustment during the study.Amendment 1.3 was submitted on 13 April 2020 and stated an endpoint on the SAE reporting until 31 days after the last visit of the last participant on the advice of the monitor.

## Data Availability

De-identified participant data and statistical code are available on reasonable request. Springer Nature remains neutral with regard to jurisdictional claims in published maps and institutional affiliations.

## Abbreviations

Amsterdam UMC: Amsterdam University Medical Centers
STN: Subthalamic nucleus
DBS: Deep brain stimulation
SAS: Starkstein Apathy Scale
MDS-UPDRS: Modified Unified Parkinson’s Disease Rating Scale
METC: Medisch Ethische Toetsingscommissie (Medical Ethical Committee)
PD: Parkinson’s disease
